### Sample size calculation

Calculation of the required sample size for the primary analysis is based on data from a Cochrane review and a large retrospective analysis [7, 32]. These studies suggest a pneumonia rate of 35% in nonoperatively treated patients and 15% in operatively treated patients with multiple rib fractures. This difference is considered clinically relevant. A two-sided test with an α level of 0.05 and a β level of 0.2 requires 72 patients in each group. In order to account for 25% loss of patients to follow-up and mortality, a sample size of 90 patients per group is needed. In total, 180 patients will be included and randomized.

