### Statistical analyses

Data will be analyzed using the Statistical Package for the Social Sciences (SPSS), version 24.0 or higher (SPSS, Chicago, IL, USA), and reported following the Consolidated Standards of Reporting Trials (CONSORT) guidelines. Normality of continuous data will be tested with the Shapiro-Wilk test. Homogeneity of variances will be tested using Levene’s test. The analysis will be performed on an intention to treat basis. A two-sided *p* value < 0.05 will be taken as threshold of statistical significance in all statistical tests. Procedures will be implemented to reduce missing data. In previous studies of the principal investigator’s department, these procedures led to < 5% missing data [54]. If necessary, missing values will be replaced using multiple imputation following the predictive mean matching method, using ten imputations.

Descriptive analysis will be performed in order to report the outcome measures for both treatment arms. For categorical data, numbers and frequencies will be reported. For continuous data, the mean and SD (parametric data) or the mean and percentiles (non-parametric data) will be reported.

Next, univariate analysis will be performed in order to test for statistical significance of differences between the primary and secondary outcome measures across the two groups. A chi-squared analysis or Fisher’s exact test will be used for statistical testing of categorical data (e.g., the primary outcome, pneumonia). Continuous data (i.e., hospital length of stay) will be tested using Student’s *t* test (parametric data; with equal variance or unequal variance whichever applies according to Levene’s test) or Mann-Whitney *U* test (non-parametric data).

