Multivariable analysis will be done as secondary analysis. A logistic regression model will be developed, with pneumonia as dependent variable and treatment as covariate. Nonoperative treatment will serve as reference category. Baseline and injury-related variables that may potentially confound the association between treatment and outcome will be included in this model as covariate. These will be selected from literature and from data of this study (see Other data collected). Known potential confounders according to literature data are the number of rib fractures and age. Other potential confounders collected as part of this study are gender, ASA, COPD, osteoporosis, and additional injuries (ISS ≥ 16 versus ISS < 16, and presence versus absence of severe injuries (AIS ≥ 3) for any body region). Variables that produce a *p* value < 0.2 in the univariate analysis will be included in the regression model. Odds ratios will be reported with their 95% confidence interval and *p* value.

Continuous outcomes repeatedly measured over time will be compared between treatment groups using linear mixed-effects regression models (with fixed effects for treatment and other covariates like gender and age, if applicable). The interaction between treatment and time will be included to test for differences between groups over time. For each follow-up moment, the estimated marginal mean will be computed per treatment group and compared post hoc with a Bonferroni test in order to correct for multiple testing.

Other continuous and binomial variables will be tested with multivariable linear and binary logistic regression models, respectively. The outcome measure will be entered as dependent variable and treatment as covariate. Nonoperative treatment will serve as the reference group. Baseline and injury-related variables that may potentially confound the association between treatment and outcome will be included in the models as covariate. Coefficients will be reported with their 95% confidence interval and *p* value.

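### The secondary adjusted pneumonia model picks its covariates by univariate p < 0.2 and does not exempt age and number of rib fractures; fix the covariates in advance

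*Protocol article*

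**What the plan says.** All of this stands in the protocol article, mostly under Statistical analyses.

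- The adjusted model has secondary status: "Multivariable analysis will be done as secondary analysis". It is a logistic regression of pneumonia on treatment plus covariates.
- On the source of the covariates: "These will be selected from literature and from data of this study (see Other data collected"). The section it points to, Other data collected, is a longer list that also holds BMI, smoking, medication use and injury mechanism, among others.
- Two factors are singled out: "Known potential confounders according to literature data are the number of rib fractures and age". A second group follows: "Other potential confounders collected as part of this study are gender, ASA, COPD, osteoporosis, and additional injuries", the last split into an ISS threshold and an AIS threshold. That makes eight named candidates.
- The entry rule is a p "value < 0.2 in the univariate analysis will be included in the regression model". No sentence says that age and number of rib fractures enter regardless.
- Earlier in the same section the term has another use: "univariate analysis will be performed in order to test for statistical significance of differences between the primary and secondary outcome measures across the two groups". There it means comparing outcomes between arms.
- Recruitment and randomization states that allocation is random, concealed, 1:1 and stratified by site, and that patients and surgeons are not blinded.

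**The concern.** Treatment is randomised, so baseline differences between arms arise by chance. The main gain from adjustment is precision, and it comes from factors that predict pneumonia. Those are best named beforehand from outside knowledge, and the protocol has already named two. A significance screen on the trial's own outcome data is a poor way to find them again with a few dozen events. It can discard a real predictor that happens to miss the threshold and keep an unrelated variable that happens to pass.

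The rule also cannot be carried out unambiguously. It is unclear what the covariates are screened against, and the pointer to Other data collected leaves the candidate list open. Two analysts could report different adjusted odds ratios from the same data, in a trial where the team knows the allocations.

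**Working it through.** **Inputs from the protocol (Sample size calculation).** "These studies suggest a pneumonia rate of 35% in nonoperatively treated patients and 15% in operatively treated patients with multiple rib fractures"; two-sided α 0.05; power 80%; 72 per group, raised to 90.

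**The plan's own figure.** With pooled variance and no continuity correction, n = [1.96·√(2·0.25·0.75) + 0.8416·√(0.35·0.65 + 0.15·0.85)]² / 0.20² = (1.200 + 0.501)² / 0.04 ≈ 72.4. Rounded up this is 73, against 72 stated. Power at 72 per group is 79.8%. The figure is reproduced.

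**Events.** 72·0.35 + 72·0.15 = 36; 90·0.35 + 90·0.15 = 45.

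**Events per parameter (intercept not counted).**
- Treatment, age, rib count: 36/3 = 12 to 45/3 = 15.
- Treatment plus all eight named candidates: 36/9 = 4 to 45/9 = 5.
- Treatment, age, rib count and 11 indicators for 12 sites: 36/14 ≈ 2.6 to 45/14 ≈ 3.2.

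**Screen against pneumonia: chance of losing a known factor.** The documents give no effect sizes, so the odds ratio (OR) per SD is assumed and varied. With an overall event rate of 0.25, SE ≈ 1/√(N·0.25·0.75), which is 0.192 at N = 144 and 0.172 at N = 180. A factor is dropped with probability about Φ(1.2816 − ln OR/SE). For OR 1.5 and N = 144 this is Φ(1.2816 − 0.4055/0.192) ≈ 0.20, and at least one of two is dropped with probability 1 − 0.80² ≈ 0.37.

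The simulations used 2,000 trials per setting, with two independent normal factors and six unrelated binary candidates:

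| OR per SD (both) | N | One given factor dropped, formula | At least one dropped, formula | At least one dropped, simulated | Power: screened vs fixed |
|---|---|---|---|---|---|
| 1.3 | 144 | 46% | 71% | 77% | 79.6% vs 81.0% |
| 1.5 | 144 | 20% | 37% | 45% | 81.1% vs 82.0% |
| 2.0 | 144 | 1% | 2% | 10% | 83.6% vs 83.6% |
| 1.3 | 180 | 40% | 64% | 69% | 86.6% vs 88.4% |
| 1.5 | 180 | 14% | 26% | 38% | 90.2% vs 91.1% |
| 2.0 | 180 | 0.3% | 0.6% | 5% | 92.0% vs 92.2% |

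With unequal effects (log-OR 0.5 and 0.35 per SD, that is OR 1.65 and 1.42) and the eight named candidates, at least one factor was dropped in 48% of trials at N = 144 and 38% at N = 180. At N = 144 the SD of the treatment log-OR was 0.474 with the screen and 0.461 with the fixed model. Power was 79.9% against 81.2%, and coverage under the screen was near 95%.

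**Unrelated candidates.** Each passes with probability 0.20. If all six others were unrelated, 6·0.2 = 1.2 would be kept on average, and at least one with probability 1 − 0.8⁶ = 74%.

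**Type I error** (OR 1.5, no treatment effect). Screened vs fixed: 5.4% vs 5.0% at N = 144, and 5.2% vs 5.2% at N = 180.

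**Screen against treatment arm.** Under randomisation each baseline factor is dropped about 80% of the time by chance, and at least one of two with probability 1 − 0.2² = 96%.

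**The case against.** The strongest reply is that little depends on this rule. The model is a declared secondary analysis, and the primary comparison is an unadjusted chi-squared or Fisher test. In simulation the screen costs at most about 2 points of power and leaves type I error and coverage near nominal. If age and rib count are strong predictors, they are seldom lost. All of that stands.

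It is also fair that the text can be read as including the literature factors and screening only the rest, since it speaks of selection from both sources. That reading is possible but not stated. It is therefore an ambiguity, not a demonstrated contradiction.

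A reader might infer more than the documents support:

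- *That the adjusted estimate is unstable or its confidence interval invalid.* The intervals do ignore the selection step, but the simulated effect is negligible at this size.
- *That some 13 candidates overload the model.* Eight are named. More terms arise only if ASA is categorical, AIS is split by body region, or further variables are drawn from Other data collected. The plan does not propose forcing every candidate in.
- *That the rule governs all the regressions.* The p < 0.2 sentence stands only in the pneumonia paragraph.

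The objection does not remove the need to change the text. The rule is stated, it is ambiguous, and a better one costs nothing in data.

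**Conclusion.** The point holds as a modest one about a secondary analysis. As written, the adjusted pneumonia model is not fixed in advance and can omit the two factors that the protocol itself considers known. With 36 to 45 events and eight named candidates, a screen against pneumonia loses at least one of them in roughly 40–50% of trials at OR about 1.4–1.65 per SD. It does so more often if the effects are weaker, and in about 2–10% of trials at OR 2 (N = 144). Read as a screen against treatment arm, it loses at least one in about 96%.

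These frequencies rest on assumed effect sizes and on independent candidates. That the covariate set depends on the data does not. The primary conclusion is not at risk. What is at stake is whether the adjusted odds ratio can be reproduced and is seen to be free of choice in an open-label trial.

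**What to change.** Delete the p < 0.2 sentence. State that the adjusted pneumonia model contains treatment, age (continuous) and number of rib fractures, whatever their significance, and settle this before outcome data are examined. Label any larger model exploratory, including one fitted in response to a chance imbalance.

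Do not add the 12 hospitals as indicator terms. In simulations at N = 144 with 12 sites and a true log-OR of −1.2, doing so moved the mean estimate to about −1.37 and raised the SD to 0.522. Some coefficient diverged in about a third of runs. If site is accounted for as the stratification factor, use a random intercept or a stratified or conditional method.

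The cost is wording only. The downside is that the main adjusted model no longer adapts to an unexpected imbalance; the exploratory model can show that instead.

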#### Secondary outcome measures

The secondary outcome measures are:Need and duration of mechanical ventilation in days. The number of days of invasive mechanical ventilation (by endotracheal tube or tracheostomy) from intubation until successful weaning will be determined. The need for mechanical ventilation will be evaluated based on arterial blood gas analysis and clinical performance of the patient. The duration of mechanical ventilation will be calculated from the dates of intubation and extubation. Re-intubation within 30 days will be recorded as well.Level of thoracic pain (NRS) and analgesics use. Thoracic pain will be determined using an 11-point Numeric Rating Scale (NRS) in which 0 implicates no pain and 10 the worst possible pain. Five thoracic pain levels will be analyzed: pain in rest, at night, during daily activities (e.g., work or hobbies), during maximal inspiration, and during self-care. Analgesics use during admission will be extracted from the medical files. After discharge, analgesics use will be asked for during the follow-up visits. Daily narcotic requirement will be calculated using an equivalence scale for 30 mg/day oral morphine.(Recovery of) pulmonary function. The parameters tidal volume (TV), forced vital capacity (FVC), inspiratory capacity (IC_lung_), and forced expiratory volume at 1 second (FEV_1_) will be determined using spirometry. Spirometry will be done by a member of the research team. During the spirometry, the patient has to inhale actively and exhale with maximum force possible. The mean of three tests will be calculated.Hospital length of stay expressed in days. This will be calculated as the time between admission and discharge from the hospital. Re-admission within 30 days will be added. Re-admission for thoracic reasons after 30 days and up to 12 months will be counted separately.ICU length of stay expressed in days. This will be calculated similarly to the hospital length of stay.Thoracic injury-related complications and mortality. The occurrence of thoracic injury-related complications will be recorded from the medical charts during clinical admission and each follow-up visit. Complications will be categorized for level of severity and treatment necessity according to the Clavien-Dindo classification [43]. Complications will include empyema (as diagnosed on CT scan, in presence of fever or positive cultures in the drained fluid), (retained) hydrothorax (a heterogeneous fluid collection with Hounsfield unit readings of 35–70 and evidence of pleural thickening) [44], nonunion (diagnosed on CT scan or operatively, at least 6 months after trauma) [45], and other (all other complications as judged by the treating physician). If mortality is caused by the thoracic injury or complication of thoracic injury, it will be counted in rates of mortality. Death caused by other reasons will be noted but excluded in this calculation.Surgery-related complications. The ORIF group can also develop hardware-related complications or failure. Hardware-related complication is superficial and deep wound infection which is defined as redness, tenderness, and warmth surrounding and in direct contact with the postoperative wound. Superficial infection leads to oral or IV antibiotics, and deep infection leads to surgical activity such as stitch removal of exploration of the wound. Hardware failure is defined as loosening of the plate, secondary dislocation of fixation material, malposition of hardware, and broken plates or splints.Secondary interventions to resolve complications. Secondary interventions within 12 months after trauma to relieve pain, treat infection, or other rib fracture-related problems will include the following: antibiotic therapy (both oral and intravenous), additional surgical interventions (e.g., surgical stabilization of nonunion, evacuation of hematoma, evacuation of empyema, removal of failed hardware, symptomatic hardware removal, and treatment of infection), and additional percutaneous interventions (e.g., for persistent bleeding intercostal artery, intraparenchymal bleeding, drainage of infection, and drainage of pleural fluid).Health-related quality of life measured using the Short Form-12 (SF-12) and EuroQoL-5D (EQ-5D) questionnaires. The SF-12 analyzes global health status, functional scale, and symptom scale. The score will be calculated based on eight domains and summarized into a Physical Component Summary (PCS) and Mental Component Summary (MCS). Data will be reported as utility score, ranging from 0 to 1 with a higher value indicating better quality of life. As a reference, the US population of 1998 will be used [46]. The EQ-5D is the most commonly used quality of life instrument for (rib) fracture patients [47, 48]. The EQ-5D is recommended for assessment of quality of life in trauma patients, especially for economic evaluation [49, 50]. The EQ-5D-5 L descriptive system consists of five dimensions of health (mobility, self-care, usual activities, pain/discomfort, and anxiety/depression), each with five possible answers. The patients’ health states will be converted into a utility score using the Dutch tariff [51]. Utility scores range from 0 to 1 with lower scores indicating poorer quality of life.Cost-effectiveness and health care consumption. Economic evaluations will be done from a societal perspective. The validated Medical Consumption Questionnaire (iMCQ) and Production Consumption Questionnaire (iPCQ) will be used. iMCQ details medical specialist care, physical therapy, hospitalization, nursing home, home care, and other costs directly associated with diagnosis, treatment, and rehabilitation. iPCQ comprises work resumption and production losses. Health care costs and lost productivity until 1 year after trauma will be measured in accordance with economic guidelines [52].

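### Every remaining binary secondary outcome goes to a multivariable logistic model whatever its event count, so for sparse or ORIF-only outcomes the adjusted odds ratio may be non-finite or uninformative

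*Protocol article*

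**What the plan says.** The Statistical analyses section has two layers for binary outcomes.

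- **Univariate step.** It covers "differences between the primary and secondary outcome measures across the two groups". For categorical outcomes, numbers and frequencies are reported by arm, and "A chi-squared analysis or Fisher’s exact test will be used for statistical testing of categorical data".
- **Multivariable step.** "Multivariable analysis will be done as secondary analysis". A logistic model is described for pneumonia. For the rest: "Other continuous and binomial variables will be tested with multivariable linear and binary logistic regression models, respectively". On covariates: "Baseline and injury-related variables that may potentially confound the association between treatment and outcome will be included in the models as covariate". Coefficients are to be reported with a 95% confidence interval and p value.

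The candidate confounders are named in the paragraph on the pneumonia model: "Known potential confounders according to literature data are the number of rib fractures and age", and "Other potential confounders collected as part of this study are gender, ASA, COPD, osteoporosis, and additional injuries", the last entered as ISS and AIS indicators. That makes eight candidates. The screen at p < 0.2 is stated for the pneumonia model and is not repeated for the other outcomes.

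Under Secondary outcome measures, the binary outcomes include empyema, retained hydrothorax, nonunion, death from thoracic causes only, and hardware complications or failure in the ORIF group. Of re-intubation the article says: "Re-intubation within 30 days will be recorded as well".

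**The concern.** The article fixes the model for every remaining binary outcome and does not make it depend on how many events occur. It gives no cap on covariates and no alternative for sparse data. The estimator is not named; ordinary maximum likelihood is the natural reading of unqualified logistic regression.

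With few events, that estimator can fail in two ways. If one arm has no events, the treatment coefficient runs to infinity and its Wald interval says nothing. If a covariate pattern separates events from non-events, that covariate's coefficient diverges, although the treatment estimate may still be finite.

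The multivariable step is also the only place where the article names an interval estimate for these outcomes, because the univariate step names a test but no effect measure. An extreme odds ratio for death, empyema or re-intubation could therefore be the one effect estimate that reaches the report.

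**Working it through.** **Group size.** The article plans for 35% versus 15% pneumonia, two-sided α 0.05 and power 80%, and states 72 per group. The pooled two-proportion formula gives 73, and power at 72 is 0.798, so the figure is reproduced to within one patient. The stated 90 is 72 × 1.25. I use 90 (all randomised) and 72 (the stated requirement) per arm.

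**Event rates.** The article gives none for individual secondary outcomes, so those below are assumptions.

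**Step 1: one arm without events.** The likelihood then keeps rising as the treatment coefficient grows, whatever covariates are present, so the odds ratio is not finite. With rates p₀ and p₁ and n per arm,

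P(no event in at least one arm) = (1−p₀)ⁿ + (1−p₁)ⁿ − (1−p₀)ⁿ(1−p₁)ⁿ.

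Example with p₀ = p₁ = 0.02 and n = 90: 0.98⁹⁰ = 0.1623, so 2 × 0.1623 − 0.0263 = 0.298. If the ORIF rate is halved, 0.99⁹⁰ = 0.4047, and 0.1623 + 0.4047 − 0.0657 = 0.501.

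| Assumed control rate | Expected events in 180 (equal rates) | Equal rates, n = 90 / 72 | ORIF rate halved, n = 90 / 72 |
|---|---|---|---|
| 1% | 1.8 | 65% / 73% | 78% / 84% |
| 2% | 3.6 | 30% / 41% | 50% / 61% |
| 3% | 5.4 | 12% / 21% | 30% / 41% |
| 5% | 9 | 2.0% / 4.9% | 11% / 18% |
| 10% | 18 | 0.02% / 0.1% | 1.0% / 2.5% |

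These figures include trials with no events at all, in which no model can be fitted.

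**Step 2: events per parameter.** Treatment plus eight covariates is nine parameters. At 90 per arm that leaves 3.6/9 = 0.4 events per parameter at 2%, 9/9 = 1.0 at 5% and 18/9 = 2.0 at 10%. With treatment plus age and number of rib fractures (three parameters) it is 1.2, 3.0 and 6.0.

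**Step 3: separation on any term.** This was simulated with 90 per arm and assumed covariate prevalences and effects.

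| Rate | Eight covariates | Two covariates |
|---|---|---|
| 2% | 94% | 30% |
| 5% | 72% | 1% |
| 10% | 38% | 0% |
| 20% | 7% | 0% |

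Most of this is divergence of a covariate, not of treatment.

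**Step 4: the treatment odds ratio itself.** With a true odds ratio of 0.5 and two or eight covariates, simulated ordinary logistic regression gave a non-finite treatment odds ratio (or no events) in 49–62% of trials at a 2% control rate, 25–39% at 3%, 10–13% at 5%, under 1% at 10% and none at 20%. These shares depend on the numerical cut-off for calling an estimate non-finite, so the exact table in step 1 is the firmer basis. Firth-penalised regression gave finite estimates, with geometric-mean odds ratios of 0.59 at 2%, 0.55–0.57 at 3%, 0.50–0.53 at 5% and 0.50–0.51 at 10%.

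**Step 5: hardware outcomes.** No assumed rate is needed. Patients without an implant cannot have these events, so the control arm has essentially none apart from crossovers, and the treatment odds ratio cannot be estimated.

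**The case against.** The case on the other side is substantial.

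- **These models are not the main comparison.** A reader might infer that the trial's safety comparison rests on them. The article does not support that: it calls them secondary and already plans counts with chi-squared or Fisher's exact tests for secondary outcomes. This stands, and confines the point to the adjusted odds ratio, its interval and its p value.
- **Low event counts are not documented.** A reader might infer that the plan itself expects them. It does not. The only background figures are high (mortality up to 34%, complications 35–77%). These are upper or pooled figures and not rates for single outcomes in a population that excludes flail chest and patients unfit for surgery, but the low rates remain assumptions.
- **False positives are not generally inflated.** A reader might expect too many significant results. In null simulations with eight covariates the likelihood-ratio test rejected in 14%, 11% and 7.6% of trials at 2%, 3% and 5%. The Wald test rejected in only 0.4%, 0.8% and 2.8%. The article does not say which test gives its p value, so inflation cannot be asserted.
- **Sparseness, more than adjustment, drives the extremes.** At 3% with no true effect, the treatment odds ratio was above 10 or below 0.1 in 17% of adjusted and 12% of unadjusted analyses. This stands: dropping covariates alone does not cure the problem.
- **Eight covariates is a worst case.** Fewer may enter, and with two there is far less separation. But nothing in the text limits the number for these outcomes.
- **A sparse-data rule could sit in an analysis plan not shown.** It could. The article nonetheless states a rule for all remaining binary outcomes, and that rule, as written, is what fails.

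**Conclusion.** The point holds within a limited scope. For sparse binary secondary outcomes, and for hardware outcomes confined to ORIF, the stated model often cannot give a usable adjusted odds ratio. The risk depends strongly on the rate. Over 72–90 patients per arm, and from equal rates to a halved ORIF rate, one arm is empty in 30–61% of trials at 2%, 12–41% at 3% and 2–18% at 5%, and the problem has nearly gone at 10%. These rates are assumed. The hardware case needs no rate, only that the outcome is put through the model as the text literally directs.

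The counts and Fisher's tests are unaffected. Nothing here bears on the pneumonia model, where the design rates imply 90 × 0.35 + 90 × 0.15 = 45 events. The change is worth making because it is cheap and prevents uninterpretable estimates from being reported, but the trial's main conclusions do not hang on it.

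**What to change.** Add a sparse-outcome rule to the multivariable part of Statistical analyses:

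1. **Define sparse in advance.** For example: no events in one arm, or too few events to support treatment plus the two literature confounders, age and number of rib fractures. Roughly 10 or fewer events in 180 patients is the region where the table above shows trouble. A cut-off of 10 events per parameter would be too broad: with nine parameters it needs 90 events in 180 patients, which would bar full adjustment even for common outcomes.
2. **For sparse outcomes, do not fit the full ordinary multivariable model.** Report counts by arm, Fisher's exact test and the risk difference with a score or exact 95% CI.
3. **If an odds ratio is wanted,** use Firth-penalised logistic regression with treatment alone or with that short prespecified covariate list.
4. **Report hardware complications and failure descriptively in the ORIF arm,** without a between-arm model.

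The cost is a few sentences, and a check that the planned software offers the penalised model. The statistical price is little or no covariate adjustment for rare outcomes and somewhat conservative tests. Randomisation already protects the comparison from systematic confounding, so the loss is small.
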